### Planned Analysis

Feasibility parameters (use, usability, and patient satisfaction) will be analyzed descriptively. Means, SD, and CIs will be reported for continuous data and counts or percentages will be reported for nominal data. The recorded interviews of patients lost to follow-up will be transcribed according to rules specified by Dresing and Pehl [59]. Patient interviews will then be analyzed with a content analysis approach [60]. The focus will be on the coding process to build categories where similarities and differences between patients will be explored [60]. MAXQDA (2022 version; VERBI Software) will be used for the analysis.

To examine the effects of the intervention, means and SDs for the primary and secondary outcomes will be reported at baseline (T0), at the end of the intervention (4 weeks; T1), at inpatient discharge, and at follow-up after 8 weeks (T2). Within- and between-groups effect sizes will be calculated using guidelines specified by Cohen [61].

Data will also be examined using inferential statistics. An intention-to-treat approach will be used. All patients who were initially assigned after randomization will be included. In a first step, baseline differences between the intervention group and the control group will be examined for all relevant variables. For metric variables, this is done using a 2-tailed *t* test for independent samples. For nominally scaled data, the chi-square test is used. In case of meaningful differences, those variables will be included in further analyses and controlled accordingly. In a second step, mixed models with “group” as the between-group factor and “time” as the within-group factor will be used to examine differences between groups. In a first analysis, a model including the study timepoints (eg, baseline, after 4 weeks, and after 8 weeks) will be calculated. In addition, an analysis including the discharge timepoint in the model will also be calculated. Specifically, the interaction between time and group will be of interest. The significance level is set at 5%.

Interviews with ward staff members will be audio-recorded and then transcribed using the guidelines specified by Dresing and Pehl [59]. Transcripts will be analyzed using thematic analysis [62] to examine ward staff experiences with the REMOTION intervention. MAXQDA software will be used for the analysis.

All quantitative analyses will be performed with the most current versions of R (R Core Team) and SPSS (IBM Corp).

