## Methods

### Study Design

Sixty patients will be randomized in a 1:1 ratio to 2 trial arms: REMOTION plus TAU and TAU alone. Assessments will take place at baseline, after 4 weeks, after 8 weeks, and after discharge from inpatient stay (Figure 1). Assessments will take place irrespective of inpatient stay duration. The planned duration of the study is approximately 2 years, to reach 60 individuals. Since external validity and the generalizability of the results to acute inpatient care settings play an important role, the inclusion and exclusion criteria are broadly defined.

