### Sample Size

Based on recommendations in the literature [33], the aim is to recruit a minimum of 30 participants per group during the trial. No power analysis is performed, as is commonly the case with randomized controlled pilot trials.

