### Procedure

After consultation with the individual ward team at the weekly interdisciplinary ward meeting, individual patients are asked about study participation. Information on the study is provided and patients are asked if they would like to participate. Once written informed consent is provided, the inclusion and exclusion criteria are checked. Eligible patients are asked to complete the baseline questionnaires online. This takes approximately 15 to 20 minutes. Randomization occurs after baseline assessment. A computerized randomization procedure concealed from the study team is used to randomize patients. Patients randomized to the intervention group receive immediate access to REMOTION. Patients in TAU are informed that they can have access after the 8-week assessment, per request. There is no blinding implemented in the study. During the study period, the ward staff is informed about a patient’s designated trial arm. Patients receive a reminder to work on the program, either face-to-face from the study team if still on the ward or by telephone or email if discharge has already occurred, once a week for 4 weeks. For individuals who fail to complete follow-up assessments, interviews on reasons for loss to follow-up will be performed via telephone. Prior to study initiation, all 4 acute ward teams are informed in detail about the study, including the provision of a 1-hour workshop on the REMOTION intervention for each ward.

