#### Primary Outcome Measure

The short version of the Brief Symptom Inventory (BSI-18) [44-46] is used to assess the primary outcome: general symptom severity. The BSI-18 contains the Global Severity Index (GSI), including all 18 items, as well as the three 6-item scales Somatization, Depression, and Anxiety [45]. The internal consistency is considered good for all 4 scales: Somatization (α=.82), Depression (α=.87), Anxiety (α=.84), and GSI (α=.93) [45]. The items are assessed on a 5-point Likert scale ranging from 0=“not at all” to 4=“very strong.” The BSI-18 is presented to patients at baseline assessment, after 4 weeks, at discharge, and after 8 weeks.

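### The group-by-time contrast for BSI-18 leaves the baseline means free in each arm, so it is unbiased but less precise than it could be, and no lead visit or model is named

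*Protocol article*

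**What the plan says.** All of this is in the protocol article. Under Primary Outcome Measure: "The BSI-18 is presented to patients at baseline assessment, after 4 weeks, at discharge, and after 8 weeks". Under Procedure: "Randomization occurs after baseline assessment".

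Planned Analysis sets out mixed models with group as the between-group factor and time as the within-group factor. "In a first analysis, a model including the study timepoints (eg, baseline, after 4 weeks, and after 8 weeks) will be calculated". A second model adds the discharge assessment. Then: "Specifically, the interaction between time and group will be of interest", and "The significance level is set at 5"%. Before these models, the arms are compared at baseline with t tests and chi-square tests, and variables that differ meaningfully are carried into the later analyses as controls.

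The same section labels week 4 the end of the intervention and week 8 follow-up. It also plans means, SDs and between-group effect sizes for the primary and secondary outcomes over baseline, week 4, discharge and week 8. No visit is called primary, and the two models are ordered but not ranked.

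On size, Study Design says "Sixty patients will be randomized in a 1:1 ratio to 2 trial arms: REMOTION plus TAU and TAU alone". Sample Size adds that "the aim is to recruit a minimum of 30 participants per group during the trial" and "No power analysis is performed, as is commonly the case with randomized controlled pilot trials".

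**The concern.** Two things are fixed less well than they could be.

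- **Baseline.** When baseline is a level of time and each arm has its own baseline mean, the group-by-time term at a later visit is the difference between arms in mean change from baseline. Randomisation after the baseline assessment guarantees that the expected baseline means are equal, and the model does not use that fact. The rule for adding covariates does not repair this. It depends on baseline tests in a randomised sample, where any difference is due to chance, so whether adjustment happens is decided by the data.
- **Lead result.** The outcome has three post-baseline assessments and two models, and nothing says which result is to be read first. The interaction over all levels of time asks whether the arms' profiles differ anywhere. It is not an effect at a stated time.

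At stake is the width of the interval around the effect estimate, and freedom to choose among results afterwards. The Discussion says the trial is meant to provide estimates of effectiveness and to inform future trials. With 60 patients precision is scarce, and this gain needs no extra patients.

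**Working it through.** **Inputs.** From the article: 60 patients, 1:1, so n=30 per arm; 5% level; post-baseline visits at week 4, week 8 and discharge. Assumed, because the article gives no values: correlation r between repeated BSI-18 scores from 0.3 to 0.8, equal SDs at all visits (set to 1), equal correlation between visits, complete data, two-sided tests. The article has no power calculation to reproduce; its only arithmetic, 2 × 30 = 60, is right.

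**Step 1: degrees of freedom.** With two groups and time as a factor, the interaction has (2−1)(3−1) = 2 df in the first model and (2−1)(4−1) = 3 df once discharge is added.

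**Step 2: variance of the between-arm contrast at one visit.**

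- As planned (difference in change): (2/n) × 2(1−r)
- Baseline constrained or adjusted: (2/n) × (1−r²)
- Ratio: (1−r²) / [2(1−r)] = (1+r)/2

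At r=0.5 the planned SE is √(2/30 × 1.0) = 0.258 SD and the adjusted SE is √(2/30 × 0.75) = 0.224 SD. The approximate 95% CI half-widths are 1.96 × 0.258 = 0.51 and 1.96 × 0.224 = 0.44 SD. The patients per arm that the planned contrast would need to match 30 adjusted are 30/ratio.

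| r | Variance ratio | SE planned | SE adjusted | Fall in SE | Planned n per arm to match |
|---|---|---|---|---|---|
| 0.3 | 0.65 | 0.306 | 0.246 | 19% | 46.2 |
| 0.5 | 0.75 | 0.258 | 0.224 | 13% | 40.0 |
| 0.7 | 0.85 | 0.200 | 0.184 | 8% | 35.3 |
| 0.8 | 0.90 | 0.163 | 0.155 | 5% | 33.3 |

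**Step 3: false positives from several answers.** In 8,000 simulated trials with no true effect, at each of r=0.3, 0.5 and 0.7:

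- either interaction test below 0.05: 6.7%, 6.9% and 6.6% (two independent tests would give 1 − 0.95² = 9.75%);
- any of the three visit contrasts below 0.05: 12.3%, 12.4% and 12.1%.

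With a sustained effect of 0.44 SD (an effect size that the Introduction cites from an earlier inpatient study, not a design assumption), the two models disagreed on significance in 11% to 14% of simulated trials.

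**Step 4: where the loss of precision comes from.** At r=0.5 and a sustained 0.44 SD, power is 40% for the planned 2-df interaction, 39% for the week-4 change contrast alone, and 49% for the week-4 contrast with baseline constrained. The loss comes from the free baseline, not from the use of an overall test.

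**The case against.** The case for leaving the plan alone is substantial.

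- **Estimates are planned.** A reader might infer that the trial would yield only two p-values. It would not: Planned Analysis commits to between-group effect sizes for the outcomes, so a significant interaction with no benefit at week 4 would be visible. What is missing is a statement of which estimate leads.
- **Baseline is used.** A reader might infer that baseline data are thrown away or that the estimate is biased. Neither is so. A change score uses baseline, and under randomisation it is unbiased. The shortfall is efficiency.
- **The overall test is not weak in itself.** For a sustained effect it costs almost nothing. If the effect grows from 0.44 to 0.58 SD, the pattern in the one cited programme with two timepoints, it has more power than the baseline-adjusted week-4 contrast (53% against 48% at r=0.5). An effect that fades after week 4 would favour the single contrast, but the article gives no reason to expect one.
- **Two models add little error.** About 7% against 5% is modest, the wording puts the three-timepoint model first, and no success rule is stated.
- **This is a pilot.** The Limitations section calls effect estimates preliminary and puts the focus on feasibility. Power figures carry little weight, and a fuller analysis plan may settle details of parameterisation and labelling.

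All of this limits the point. It does not remove the precision argument, because the article does state a method and a rule for adjustment, and a more precise valid method is available for the same patients.

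**Conclusion.** The point holds as one of efficiency and clarity, not of validity. The planned visit contrast has a variance 1/0.90 = 1.11 to 1/0.65 = 1.54 times that of the constrained or adjusted one for r from 0.8 to 0.3. At r=0.5 that is an SE of 0.258 against 0.224 SD with 30 per arm. The gain is worthwhile at r of 0.3 to 0.5 and small at 0.8. It rests on an assumed r, equal variances and complete data; dropout would change the figures.

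The missing lead visit and the unranked models are a secondary matter: about 12% false positives from choosing among three visits and about 7% from choosing between two models. In an exploratory pilot the harm is selective reading, not a failed confirmatory test. The article does not support saying that the interaction test should be rejected for lack of power.

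**What to change.** Reword Planned Analysis as follows.

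1. In every model for BSI-18, constrain the baseline mean to be common to both arms. Equivalently with complete data, use baseline BSI-18 as a covariate with its own slope at each visit and only post-baseline visits as responses. Treat the other outcomes measured at baseline in the same way. This replaces the rule that adds variables after baseline tests.
2. Report the model-based between-arm difference with its 95% CI at each fixed visit.
3. Name one lead visit in advance. Week 4 is the natural choice, because the plan labels it the end of the intervention; week 8 is then secondary.
4. Label the model with discharge as supportive. The caption to Figure 1 allows discharge at any time after randomisation, so it has no fixed place on the time scale, and controls may ask for the programme after week 8.

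The cost is wording only: no extra patients or assessments. The downside is that an effect emerging after week 4 would not be the headline result, although it would still be reported with its interval.

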### Ethical Considerations

The study has been approved by the Ethics Committee of the Canton of Bern, Switzerland (2020-01139). Informed consent is obtained from all participants. The trial is registered with clinicaltrials.gov (NCT04990674). The study will be conducted according to local regulations and the Declaration of Helsinki. The CONSORT-EHEALTH (Consolidated Standards of Reporting Trials for e-Health) [63] checklist will be followed in reporting the trial. Participants receive no compensation for taking part in the trial.

## Results

Recruitment for the study started in August 2021. As of March 2023, it was still ongoing. Results for the study are expected in 2024.

## Discussion

### Expected Findings

While a few trials on blended treatment in inpatient care exist, patients in the acute psychiatric inpatient setting are understudied, and there is a need for the examination and evaluation of internet-based interventions in this specific setting. This randomized controlled pilot trial explores a web-based emotion regulation intervention in this treatment setting. The study is designed to obtain information on the feasibility of the intervention. It is also designed to provide estimates of the effectiveness concerning reduction of symptom severity and improvement of emotion regulation. The study will inform future trials on blended treatment (ie, the combination of internet-based interventions with face-to-face treatment) in acute psychiatric inpatient care and thus provide evidence on the potential added value of a web-based intervention in this specific setting.

### Limitations

This is a randomized controlled pilot trial, and the targeted sample size is small. All estimations of possible effects on symptom severity and emotion regulation are thus preliminary only. The focus of the study lies with feasibility. As there are only a few studies on internet interventions in acute psychiatric care, the study is inherently exploratory. Several components of the specific acute psychiatric inpatient care setting may be challenging for study feasibility: recruitment of more severely impaired patients, fast turnaround on wards, the possibility of conversations between patients from different trial conditions on one ward, and multiple stakeholders being involved in treatment. We have tried to consider these factors by providing an adequate study duration; informing ward staff in detail about the study prior to commencement, including the fact that the TAU group should not receive information on REMOTION content; and by incorporating weekly reminders to work on the intervention, even if patients have been discharged.

### Conclusion

This randomized controlled pilot study is the first to examine a web-based emotion regulation intervention, REMOTION, in acute psychiatric inpatient care at a public university hospital. This type of blended treatment is grossly understudied. The results of the study will provide information on the potential added value of such an intervention for patients with severe mental health disorders in acute psychiatric care.

## Abbreviations

BSI: Brief Symptom Inventory
CSQ: Client Satisfaction Questionnaire
DERS: Difficulties in Emotion Regulation Questionnaire
EPM: extended process model
GSI: Global Severity Index
REMOTION: Regulate Emotion
SEK: Fragebogen zur standardisierten Selbsteinschätzung emotionaler Kompetenzen
SUS: System Usability Scale
TAU: treatment as usual
UPD: Universitäre Psychiatrische Dienste
ZUF: Fragebogen zur Patientenzufriedenheit
